## Abstract

Breast cancer impairs physical and psychological well-being, even some years after treatments. Oncological treatments can strongly affect the body due to scars and breast(s) removal, for example, increasing symptoms of anxiety and depression. Psychological studies are effective in improving breast cancer survivors’ emotions and behaviors through several approaches to interventions. Over years, the Mindfulness-Based Stress Reduction (MBSR) has been evaluated as an effective intervention to promote well-being in breast cancer survivors. The present study protocol aims to evaluate the effectiveness of a MBSR intervention in regulating interoceptive sensations, as the ability to be aware of inner sensations. Second, it seeks to identify changes in interoceptive feelings, mood, and body perception following the intervention. These changes will be evaluated across three data collection times to assess differences about emotions and body perception over time, focusing on their relevance for breast cancer survivors’ well-being. Finally, the present study protocol aims to detect improvements in anxiety, depression, and body awareness, considering the potential positive impact of the MBSR approach on emotional well-being. Direction for future psychological intervention are given.

## Introduction

Most women with breast cancer have to deal with diagnosis and its related oncological treatments as a very difficult experience to accept, starting with the consequences on their Quality of Life (Schell et al., 2019). Oncological treatments (e.g., chemotherapy, radiotherapy, immunotherapy) can damage the body due to the presence of scars, hair loss, and breast(s) removal, for example (Fioretti et al., 2017). Therefore, patients generally report high levels of distress, anxiety, depression, physical symptoms of pain, fatigue and sleep–wake rhythm dysfunction, even several years after finishing treatments (Abrahams et al., 2018). Concerning emotional issues, it is mandatory to address the bodily self, defined as an expression of implicit knowledge about physical actions and movements (Sebri et al., 2021). Addressing bodily self is particularly relevant for breast cancer survivors, who concern changes in body image perception due to altered weight, possible hair loss, and the sudden onset of menopausal symptoms (Pintado and Andrade, 2017; Sebri et al., 2022). Additionally, body perception and body image are strictly tied to social and intimate relationships. Following the Discrepancy Theory by Higgins (1987), when there is a significant gap between one’s current and the desired body, it can lead to feelings of dissatisfaction and emotional distress. This discrepancy can severely impact women’s sense of femininity and sexuality (Male et al., 2016). Moreover, one’s own body after diagnosis and oncological treatments can be experienced as ill and damaged, even perceiving them as a source of danger for the fear of cancer recurrence. This can increase the risk of being labeled as “patients” rather than “persons,” reinforcing this type of self-definition and representation (McGannon et al., 2016). To improve levels of psycho-emotional well-being, the literature highlights the effectiveness of multimodal interventions aimed at improving both self-image perception and psycho-social aspects (Lengacher et al., 2009). Current studies demonstrated the efficacy of complementary and alternative interventions in groups of breast cancer survivors to improve positive social support (Durosini et al., 2021; Sebri et al., 2023; Sebri and Pravettoni, 2023). More specifically, numerous studies show the effectiveness of integrating standardized techniques and complementary medicine therapies, with a view to a multidisciplinary approach. Among them, one method effectively applied in the oncology field, and specifically in breast cancer patients (Carlson et al., 2004; Henderson et al., 2013), is the application of the Mindfulness-Based Stress Reduction (MBSR) protocol developed by Kabat-Zinn (1979).

Mindfulness is defined as paying attention to the unfolding of experience moment by moment, with intention and in a non-judgmental manner (Segal et al., 2014), cultivating a stable and non-reactive awareness even in stressful situations, such as that induced by a course of illness (Guu et al., 2023). Mindfulness allows one to pause ruminating thoughts, and access a greater awareness of one’s mental habits and related bodily sensations (Mehling et al., 2009; Pintado and Andrade, 2017). In this regard, the perception and awareness of what is happening within the body (e.g., concerning a general feeling of pleasantness/unpleasantness) is referred to as interoception (Barrett, 2017). Most Mindfulness-based protocols permit to cultivate interoceptive awareness, which plays a crucial role in the effectiveness of mindfulness-based interventions (Fischer et al., 2017), allowing the practitioners to shift attention from thinking about one’s bodily sensations to immediately feeling them (Farb et al., 2015; Mehling et al., 2017). Indeed, mindfulness can improve the relationship with interoceptive signals, encouraging more adaptive behaviors toward bodily sensations and reducing experiential avoidance (Weng et al., 2021). Accordingly, individuals who have practiced mindfulness report changes in their interoceptive awareness, having learned to redirect attention to their body, manage stress, regulate emotions and facilitate cognitive insight into their body/emotional state (de Jong et al., 2016; Fissler et al., 2016). Furthermore, enhanced interoception is also linked to improved mental health outcomes, making it a relevant and valuable capacity targeted in MBSR interventions for breast cancer patients.

Increased emotional awareness is indeed associated with a decrease in somatic symptoms (such as nausea, pain and fatigability) and distress, as well as a subsequent reduction in mortality in breast cancer patients (Czamanski-Cohen et al., 2019). Specifically, previous studies noted increased vitality, decreased physical pain, improvements in both mood (e.g., anxiety and depression) and social functioning (Reibel et al., 2001). The MBSR program also facilitates other ways of taking care of oneself (e.g., more rest and physical activity), paying attention without evaluation or judgment (Glynn et al., 2020). Accordingly, it provides greater benefits compared to usual care across all diagnoses, except for cognitive-behavioral therapy that is considered more efficacy in some specific cases (e.g., pain management) (Pardos-Gascón et al., 2021). Comparisons between mindfulness interventions are scarce, with MBSR being the most studied. In central sensitization syndromes, variables associated with pain tend to improve with treatment (Pardos-Gascón et al., 2021). Finally, regarding body perception, some studies report greater acceptance of oneself and one’s body after MBSR interventions (Luiggi-Hernandez et al., 2018; Penlington, 2019; Tate et al., 2018; Visser et al., 2015). Indeed, the effectiveness of MBSR programs about changes in body image perception is noted, highlighting how increased awareness can positively impact self-image. In this regard, a study by Pérez-Peña et al. (2022) highlighted the impact of mindfulness on proprioception within the body image perception. Proprioception is defined as the perception of body movement and position. It depends on both psychological (e.g., memory and learning) and physiological processes (e.g., mechanosensory neurons throughout the body known as proprioceptors) (Tuthill and Azim, 2018). Similar to interoception, proprioception is largely unconscious, although some proprioceptive information can be brought into conscious awareness (Pérez-Peña et al., 2022).

Even though the cancer experience causes quite a few issues related to the perception of self and one’s internal states, few programs specifically aimed at improving body image have been developed so far (Pintado and Andrade, 2017; Pidgeon and Appleby, 2014). To date, few studies have analyzed the effectiveness of MBSR programs in treating body image in breast cancer patients. In a recent randomized trial (Pintado and Andrade, 2017), patients who followed an MBSR protocol reported a decrease in negative thoughts and emotions related to self-image perception, an increase in positive thoughts, and increased body awareness. However, the scientific literature has so far not focused on measuring the effectiveness of MBSR protocols on interoceptive awareness in breast cancer patients. The overall aim of the present study is to evaluate the effectiveness of a MBSR intervention in regulating interoceptive feelings in women with breast cancer experience. This study will highlight possible changes in emotions and body perception in breast cancer survivors. Specifically, we aim to identify predictive aspects of the intervention on interoceptive feelings, mood, and body perception according to the three data collection times. In addition, we expect to be able to detect an improvement in mood (anxiety and depression) and body awareness (medium-term benefit).

## Methods

The present protocol was obtained from a licensing committee from a University that approved the study. Additionally, all participants signed the informed consent form. Lastly, this study follows the Declaration of Helsinki and method design will be carried out in accordance with relevant guidelines and regulations. Participants who belong to breast cancer associations will be contacted and invited to take part in this project by email. If they will accept, an informed consent before starting the first meeting will be sent.

The inclusion criteria for participation in the study are as follows:

Age between 30 and 50 to guarantee the sample homogeneity;Patients with the first diagnosis of stage I, II, and III breast cancer;Patients who have experience of previous surgery as an oncological intervention to remove cancer.Patients who have received chemotherapy and completed treatment. Only chemotherapy can be accepted as the oncological treatments, not immunotherapy or radiotherapy. This criterion is chosen to ensure the homogeneity of the sample and to focus on patients who are not in an advanced stage of therapy but have completed their treatments.Fluently understand and speak the Italian language.

Exclusion criteria are related to:

Metastatic disease, meaning the need to treat other types of cancer in addition to breast cancer;Patients with a previous cancer diagnosis who have developed other types of cancer, different from breast cancer;Patients who are undergoing psychological treatment, whether individually or in groups. It is relevant to ask them if they are currently participating in a psychological intervention, especially if it involves processing of cancer-related issues;Presence of neurological deficits and/or psychiatric disorders that could impair rationale participation to the study;Lack of knowledge of the Italian language, which could affect the full and accurate understanding of both the mindfulness practice and the questionnaires’ contents.

This study will last approximately 6 months and will use a quantitative research methodology, with a between-subjects design. Forty participants meeting the inclusion and exclusion criteria set out above will be enrolled and randomly distributed through Excel software (RAND function) into the following two groups:

*Experimental group*: participants who will be immediately included in the MBSR protocol;*Waitlist control group*: participants who will be included in the MBSR protocol after 12 weeks from the start of the protocol.

The intervention proposed to the experimental group will be conducted by a psychologist expert in the MBSR protocol. The MBSR intervention will be structured as follows: it envisages eight weekly group meetings lasting about 2/2.5 h each, plus an intensive meeting (generally proposed between the sixth and seventh meetings or between the seventh and eighth meetings), which lasts about 5 h. Moreover, a follow-up meeting about a month after the conclusion of the course will be proposed. Participation in the course is preceded by an acquaintance and information meeting with the trainer who will be the course leader (40 min). The program will be experiential; participants do not passively receive guidance on how to manage stress but become active participants through systematic training in mindfulness practice. Specifically, based on the definition of mindfulness, the MBSR protocol invites people to cultivate awareness through meditation and teach how to enter into a different relationship with suffering, regardless of the specific causes, whether medical or psychological. It is possible to hypothesize that insights gained during meditative practice could serve as a basis for developing effective strategies for managing chronic pain conditions (Giommi, 2006).

The study will take place in a brightly lit and spacious room. This room will be specifically dedicated to accommodate group sessions, mindfulness exercises and group practices, with ample space for participants to either sit on the floor or use chairs, ensuring comfort and flexibility. All sessions will consistently be conducted in this same room, providing a stable and familiar environment for participants throughout the study.

On a practical level, the MBSR protocol will include (see Table 1 for a detailed schedule of meetings):

Moments of formal practice (sitting meditation with a focus on breath, body, sound, and mind content; body scan; mindful movement; walking meditation. These points will be discussed in detail below);Free sharing of experiences and inquiry;Formal practice to be performed daily at home with the support of audio tracks;Informal practice (bringing awareness into everyday actions that we generally repeat daily according to automatic patterns);Printed material to support formal and informal practice.The formal and informal practice that the participant will be invited to perform daily takes approximately 40 min per day.

**Table 1 tab1:** Detailed description of the proposed meetings.

**Meeting**	**Activity**
**Session 1**	The first session will focus on presenting the activities to all participants and then introducing preliminary exercises to start the practice. Specifically: The facilitator will share preliminary directions and instructions with the group. A brief period of silence will follow A brief introduction to the definition of mindfulness will be provided to ensure participants understand its content Initial exercises will include a body scan followed by an inquiry, and participants will be guided to focus on their breath for 3-4 minutes The facilitator will assign homework related to the activities covered in the session The session will conclude with a final moment of silent reflection
**Session 2**	In the second session, participants will first be invited to practice the activities learned previously. Following this, additional mindfulness content will be introduced, as outlined below: After a brief introduction to the session's content and objectives, participants will engage in a body scan practice. They will then have the opportunity to discuss any questions about the body scan exercise performed at home and during the session, to enhance the effectiveness of the activity Next, the facilitator will guide participants in developing conscious awareness of their physical movements and sensations. Participants will be encouraged to ask questions, and then triads will be formed to discuss informal practices (e.g., brief exercises for individual practice at home) A group sitting meditation focused on breath awareness will be conducted for 15 minutes The facilitator will assign homework related to the activities covered in the session. In particular, participants will be invited to compile a diary with their "pleasant events" in the next days The session will conclude with a final moment of silent reflection
**Session 3**	In the third session, additional mindfulness content will be introduced and practiced in groups. Specifically: The session will begin with a brief introduction to its content and objectives. The psychologist will then lead a 20-minute seated meditation, focusing on body and breath. Afterward, participants will have the opportunity to discuss any questions about the formal practice they have completed at home. Participants will then engage in a 20-minute walking meditation. Next, a group discussion will be held to reflect on and share individual experiences of the previous practices. Triads will then take turns sharing from their "pleasant events" diary, compiled throughout the week. The psychologist will introduce the "triangle" map of mindfulness, a psychoeducational technique, to enhance understanding. The facilitator will assign homework related to the activities covered in the session The session will conclude with a final moment of silent reflection
**Session 4**	In the fourth session, participants will engage in additional mindfulness practices as follows: The session will start with a brief introduction to its content and objectives. The psychologists will then lead a 30-minute sitting meditation, focusing on body, breath, and sound. Participants will have dedicated time to discuss any questions about the formal practice they completed at home A new practice will be introduced, specifically standing and/or floor yoga Triads will take turns sharing from their "pleasant events" diaries, compiled over the past week A designated time will be allocated for discussing inquiries about unpleasant events, with a focus on identifying 'symptoms in the body' The psychologist will conduct a psychoeducational training on the stress response (first part) The facilitator will assign homework related to the activities covered in the session The session will conclude with a final moment of silent reflection
**Session 5**	In the fifth session, no new exercises will be introduced. Instead, participants will be encouraged to reinforce the valuable activities they have already learned. Additionally, the session will focus on discussing individual responses to stressful events and exploring appropriate strategies, as follows: The session will start with a brief introduction to its content and objectives. The psychologists will then lead a 40-minute sitting meditation, focusing on body, breath, and sound. Participants will have dedicated time to discuss any questions about the formal practice they completed at home Next, a group discussion will be held to reflect on and share individual experiences of the previous practices. Triads will then take turns sharing from their "pleasant events" diary, compiled throughout the week. In particular, participants will be invited to reflect on their reaction to stressful events, rescuing the information collected in the fourth session The psychologist will conduct a psychoeducational training on the stress response (second part) The facilitator will assign homework related to the activities covered in the session The session will conclude with a final moment of silent reflection
**Session 6**	The session will start with a brief introduction to its content and objectives. The psychologists will then lead a 40-minute sitting meditation, focusing on body, breath, and sound. Participants will have dedicated time to discuss any questions about the formal practice they completed at home Next, a group discussion will be held to reflect on and share individual experiences of the previous practices. Triads will then take turns sharing from their "pleasant events" diary, compiled throughout the week. In particular, participants will be invited to reflect on their communication with others, as a new focus of interest The facilitator will propose the first interpersonal awareness exercise, which have to conducted in pairs The facilitator will assign homework related to the activities covered in the session The session will conclude with a final moment of silent reflection
**Session 7**	This session will specifically focus on the second exercise related to interpersonal awareness, in addition to the usual practice of meditation and breath awareness. Participants will be invited to: The session will start with a brief introduction to its content and objectives. The psychologists will then lead a 40-minute sitting meditation, focusing on body, breath, and sound. Participants will have dedicated time to discuss any questions about the formal practice they completed at home Next, a group discussion will be held to reflect on and share individual experiences of the previous practices. Triads will then take turns sharing from their "pleasant events" diary, compiled throughout the week. In particular, participants will be invited to reflect on their communication with others, following the contents and reflections shared in the previous sessions The facilitator will propose the second interpersonal awareness exercise, which have to conducted in pairs The facilitator will assign homework related to the activities covered in the session The session will conclude with a final moment of silent reflection
**Session 8**	In the eighth and final session, participants will engage in new meditative exercises suitable for individual practice. Additionally, a final discussion about the program's content will be held. Specifically: The session will begin with a brief introduction to its content and objectives The psychologists will then lead a 40-minute body scan exercise Following this, the psychologists will conduct a session focusing on body, breath, sounds, thoughts, and open awareness. Participants will have time to discuss any questions about the formal practices completed at home After a brief summary of the course by the instructor, there will be a discussion on personal practice following the conclusion of the protocol, including inquiries about obstacles and motivations for continuing. The instructor will encourage individual self-reflection on the experience and significance of the course The session will conclude with a brief meditative writing exercise lasting approximately 10-15 minutes The session will conclude with a final moment of silent reflection

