## Data analysis and sample size

The sample size required for the present study was calculated using G∗Power 3.1.9.2 software (Faul et al., 2007), for an analysis of variance with repeated measures (ANOVA) with interaction. The primary endpoint will be the difference between the two experimental groups (i.e., between-subjects factor) in the improvement of the overall MAIA scale score at pre-intervention (T0), post-intervention (T1), and follow-up (T2) times. To detect a weak-median effect size (i.e., partial η2 = 0.04), the required sample size is 40 (i.e., 20 participants in each experimental group). The type I error rate (*α*) was set at 0.05 (two-sided) and the power (1 - *β*) was set at 0.90. The collected data will be analyzed using the statistical analysis software Statistical Package for Social Science (SPSS, version 27.0).

Adherence to the intervention will be monitored and reported in the results, and data from participants who do not adhere will be managed using an intention-to-treat analysis.

The data collected in this study will be analyzed using repeated measures ANOVA to compare the outcomes between the experimental and control groups across the three time points. The primary analysis will focus on changes in the overall MAIA scale scores, allowing us to evaluate the main effects of time and group as well as the interaction between these factors. Secondary exploratory analyses will include repeated measures ANOVAs on the individual MAIA subscales and additional psychological outcomes such as anxiety, depression, and body image perception. Effect sizes and confidence intervals will be reported alongside *p*-values to offer a comprehensive understanding of the observed effects.

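### MBSR is delivered in groups in one arm only, but the sample size and the primary ANOVA assume independent women; if course groups are correlated, precision and power are overstated

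*Protocol article*

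**What the plan says.** **Delivery (Methods).** Women are randomised individually to immediate MBSR or to a waitlist. For the MBSR course, "it envisages eight weekly group meetings lasting about 2/2.5 h each", plus an intensive meeting of about five hours and a follow-up meeting about a month after the course ends. The intervention "will be conducted by a psychologist expert in the MBSR protocol". Table 1 builds interaction into the sessions: group discussion, triads and, in sessions 6 and 7, exercises in pairs.

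**Timing (Methods; Evaluation tools).** The waitlist arm enters MBSR 12 weeks after the start. Both arms are assessed before the intervention (T0), at 8 weeks (T1) and at 12 weeks (T2).

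**Analysis and size (Data analysis and sample size).** "The data collected in this study will be analyzed using repeated measures ANOVA to compare the outcomes between the experimental and control groups". The primary analysis concerns the overall MAIA score, with effects of time, group and their interaction. The sample size was computed "for an analysis of variance with repeated measures (ANOVA) with interaction", for a partial η² of 0.04 at two-sided α 0.05 and power 0.90, and "the required sample size is 40 (i.e., 20 participants in each experimental group". Neither the model nor the calculation has a term for course group. The number and size of the course groups are not given.

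**The concern.** Women who attend the same course share its meetings and influence one another in discussion, triads and pairs. Their outcomes after T0 may therefore resemble each other more than those of unrelated women. The documents describe no such shared treatment for the waitlist arm before T2, so any correlation that the course creates sits in one arm only.

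Repeated-measures ANOVA allows for correlation within one woman over time. It does not allow for correlation between women in the same course group. With positive correlation between them, 20 MBSR women carry less information than 20 independent women. The reported interval is then too narrow and the p-value too small, and N = 40 does not deliver the stated power. A group that happened to go well or badly could be read as the effect of MBSR on the primary endpoint.

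**Working it through.** **Inputs from the article.** 20 women per arm; two-sided α 0.05; power 0.90; partial η² 0.04; three time points; group treatment in the MBSR arm only.

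**Assumed, because the article gives neither.** Intraclass correlation (ICC) within a course group of 0.01, 0.02, 0.05 or 0.10; course groups of m = 20, 10 or 5.

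**1. The plan's own figure.** Cohen's f = √(0.04/0.96) = 0.204. For the within-between interaction, the noncentrality is λ = N·3·f²/(1−ρ) with 2 and 2(N−2) degrees of freedom, where ρ is the correlation between repeated measures. With ρ = 0.5, the required N is 54 and the power at N = 40 is 0.80. N = 40 gives 0.90 only at ρ of about 0.62, which the article does not state. That is a separate matter. What counts here is that no version of this calculation contains clustering.

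**2. Variance of the arm difference.** With a design effect in the MBSR arm only, the variance relative to independence is

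[(1 + (m−1)·ICC) + 1] / 2.

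| ICC | m = 20 | m = 10 | m = 5 |
|---|---|---|---|
| 0.01 | 1.10 | 1.05 | 1.02 |
| 0.02 | 1.19 | 1.09 | 1.04 |
| 0.05 | 1.48 | 1.23 | 1.10 |
| 0.10 | 1.95 | 1.45 | 1.20 |

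Example: m = 20 and ICC 0.05 give (1.95 + 1)/2 = 1.475.

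**3. Type I error, normal approximation, one group of 20.** 2·(1 − Φ(1.96/√inflation)) = 0.061, 0.072, 0.107 and 0.160 for the four ICCs.

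**4. Type I error of the planned interaction test.** Simulation of the 2 × 3 repeated-measures ANOVA: 20,000 runs per setting, 20 per arm, no average treatment effect, and a shared group effect at T1 and T2 in the MBSR arm only. Each cell gives the result for ρ = 0.5, then for ρ = 0.6.

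| ICC | one group of 20 | two of 10 | four of 5 |
|---|---|---|---|
| 0 | 0.049, 0.050 | 0.050, 0.050 | 0.048, 0.050 |
| 0.01 | 0.061, 0.061 | 0.056, 0.055 | 0.052, 0.051 |
| 0.02 | 0.073, 0.073 | 0.057, 0.061 | 0.052, 0.059 |
| 0.05 | 0.106, 0.121 | 0.075, 0.082 | 0.060, 0.063 |
| 0.10 | 0.171, 0.201 | 0.106, 0.123 | 0.074, 0.083 |

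With no clustering the test holds its 5% level, so the excess comes from the group effect.

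**5. Sample size equivalent at ICC 0.05.** Groups of 10: 40 × 1.225 = 49, so about 50 with equal arms. Groups of 20: 40 × 1.475 = 59, so about 60. This scaling takes the plan's 40 as given.

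**6. How much of the standard error is missed.** The ANOVA also loses the between-group part of the MBSR variance. For one group of 20, a single post-treatment score and equal total variance in both arms, the true over the reported standard error is √{[(1 + 19·ICC) + 1] / [(1 − ICC) + 1]}:
- ICC 0.01: √(2.19/1.99) = 1.05
- ICC 0.05: √(2.95/1.95) = 1.23
- ICC 0.10: √(3.90/1.90) = 1.43

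**The case against.** Several points on the other side are sound.

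- **The inflation is conditional.** It needs a positive ICC, and its size depends on a group layout that the article does not give. With four groups of 5 and an ICC of 0.02 or less it is negligible. A reader might infer that the type I error is certainly too high, or that all 20 women form one group. The documents establish neither.
- **It depends on the null hypothesis.** Women are randomised individually. If the course affects no one at all, it cannot create correlation, and the ordinary test is sound. The excess applies to the null of a zero average effect over course groups like these. That is the relevant target if the result is to speak for MBSR in general, but it is a choice and should be stated.
- **Sharing does not span T0.** T0 precedes the course, so the group effect belongs at T1 and T2 only.
- **Contact among waitlist women is not described.** A reader might infer that they never meet. The article says only that they start MBSR later, and it recruits through breast cancer associations, so contact in either arm is unknown.
- **The trainer is a separate matter.** A reader might count the single psychologist as a cause of the small standard error. A trainer who is the same for the whole arm adds no variance within it; that trainer is confounded with treatment and limits generalisability. Nor is a single trainer certain: Methods uses the singular, while Table 1 uses the plural in sessions 4 to 8.
- **A mixed model is no full cure.** With two groups of 10, the group variance would be estimated as zero in about 63%, 57% and 50% of trials at ICC 0.02, 0.05 and 0.10. In a single-outcome simulation at ICC 0.10, a partially nested test with a normal reference still rejected about 8.6%, against 10.9% without the adjustment. With one group, no model separates group from treatment.
- **The analysis plan is not shown.** Group numbers and clustering sensitivity analyses may be there. But the article itself fixes the primary model, its terms and the sample size, and all three rest on independence.

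These points limit the claim and shape the remedy. They do not remove the mismatch between delivery and analysis.

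**Conclusion.** The concern holds in conditional form. Treatment is delivered in interacting groups in one arm only up to the last assessment, while the stated sample size and primary ANOVA treat every woman as independent. For any positive within-group correlation, the standard error is too small, the power of 0.90 is overstated, and the type I error for a zero average effect across course groups exceeds 5%.

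The size rests on assumed ICCs and group layouts. Over ICCs of 0.01 to 0.10 it ranges from almost nothing (four small groups, low ICC) to three or four times the nominal level (one group of 20, ICC 0.10). The trainer issue bears on confounding and generalisability, not on the standard error. This should be corrected in the analysis and reporting; it does not invalidate the trial.

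**What to change.** 1. Record each woman's course group and trainer while the courses run, and state the number and size of groups. Reconcile the singular and plural references to the psychologist.
2. If there are several groups, fit a partially nested mixed model with a random course-group effect at T1 and T2 in the MBSR arm only, and with small-sample degrees of freedom.
3. If there is one group, or too few to estimate the group variance, report the primary estimate with its standard error inflated for assumed ICCs of 0.01, 0.05 and 0.10. Call this a sensitivity analysis, not a correction, and limit the conclusion to this group and trainer. The factors 1.05, 1.23 and 1.43 in step 6 apply to one group of 20 and a single post-treatment score. For a change or interaction contrast, compute them on that scale.
4. State that N = 40 and power 0.90 assume zero clustering.

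**Cost.** Record-keeping, analysis and wording; no extra participants, staff or sessions. With few groups the intervals may widen considerably.
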